Emerge of coronavirus SARS-CoV-2 pneumonia (COVID-19) in Wuhan, China in 2019, and it posterior spread to the world, has exposed an overloaded health system in many regions. COVID-19 has been associated to variable clinical presentation and prognosis as preliminary reports are published (7–9). Available data indicates that most part of the cases were pausi- or asymptomatic, as mild forms of the disease are expressed. Report for New York (9) described the initial evolution of 5700 patients, 373 of whom (14.2%) needed intensive care admission, and 320 (12.2%) required mechanical ventilation. However, mortality under mechanical ventilation was 88.1%, and ARDS was probably the cause to initiate ventilatory support. In the Lombardia case-series (7), 1150/1591 critically ill patients needed mechanical ventilation, probably due to ARDS. These data indicate that the severe ill patients with SARS-CoV-2 infections usually require mechanical ventilation for long-periods, and their prognosis is worse.

Several treatment options had been tried since the initial description of COVID-19, such as antiviral, immunomodulators drugs, and immunotherapy. No treatment has shown a clear benefit at the present time. Lopinavir/ritonavir, a protease inhibitor for HIV, was evaluated in a randomized open trial, with no placebo, in in-patients with severe pneumonia (10). No significant differences were seen in the primary outcome (time to recover), though, it decreased the length of stay in intensive care. Remdesivir, an antiviral drug designed to treat Ebola, has shown in-vitro activity against SARS-CoV-2, and decreased the hospital length of stay without affecting mortality. Chloroquine has been used in SARS 2012 epidemic, due to activity against SARS-CoV. Preliminary reports suggested that hydroxychloroquine shorten viral shedding time in mild disease, especially in combination with azithromycin (11). Convalescent plasma has been evaluated in small series and one unconcluded randomized clinical trial with encouraging results (12,13). On the other hand, immunomodulatory therapies, such as steroids, interferon or antibodies against interleukine-6, had been proposed to treat the cytokine storm associated to coronavirus severe disease.

Systemic steroids have been the immunosuppressant drugs most used against COVID-19, in opposition to the initial recommendations (14). The inflammatory response in the acute phase and the frequent use of steroids in pulmonary interstitial diseases are the probably reasons for its use. However, there is concern in the medical community about the generalized use of immunosupressors (above all steroids) in COVID-19 infections. The efficacy of systemic steroids has been highly controversial in viral pneumonias prior to this pandemic. It is known that, in general, these drugs reduce lung inflammation but also inhibit the immune response and clearance of the pathogen. The fear of a negative effect on viral replication, and the increase of hospital infection spread, are the main reasons for avoidance of corticosteroid prescription. These concerns are based in low quality observational and heterogeneous studies of influenza pneumonia, as indicated in a Cochrane review (15). However, some authors sustained that the inflammatory response is the main factor related to patient prognosis, with no relationship to viral shedding (16), and they recommended in favor of the utilization of steroids in severe cases.

The utility of steroids in the treatment of ARDS has been controversial for years. A recent statement of the SCCM (Society of Critical Care Medicine) and the ESICM (European Society of Intensive Care Medicine) suggest the utilization of methylprednisolone for 14 days in patients with early ARDS (17). This recommendation was based on the positive results in mortality and duration of mechanical ventilation of 4 clinical studies. Recently, Villar and cols published the results of a multicentre study performed in Spain, in which moderate to severe ARDS patients were randomized to dexamethasone (20 mg qd for 5 days followed by 10 mg qd for 5 days) against placebo (18). A decrease in hospital mortality (21% vs. 36%) and shorten in ventilators days (4.8 days difference) were reported with the use of dexamethasone. Main cause of ARDS in the study was pneumonia. Additional advantages of dexamethasone, in opposition to other steroids, are the administration period (once a day) and the lack of mineralocorticoid effect.

The Surviving Sepsis Campaign COVID-19 panel supported a weak recommendation to use steroids in the sickest patients with ARDS due to SARS-CoV-2 (19). Cochrane could not issue a report on the benefits of steroids, due to the absence of evidence in patients with COVID-19, and asked for time until the results of ongoing trials (19). A recommendation against the general use of steroids in patients with COVID-19 was initially issued by the NIH (National Institute of Health), the WHO (World Health Organization), the CDC (Center for Disease Control), and the IDSA (Infectious Disease Society of America), due to the absence of clear evidence (20,21).

Recently, the RECOVERY trial provides evidence that treatment with dexamethasone at a dose of 6 mg once daily for up to 10 days reduces 28-day mortality in patients with Covid-19 who are receiving respiratory support (22). This British study compared multiple treatments for COVID-19 in a randomized, open label trial, with a complex design, in patients with different severities. This sub study randomized 6425 patients (ratio 1:2) to received dexamethasone 6 mg/day for ten days against placebo. A decreased in 28-days mortality (21.6% vs. 24.6%) was seen as main outcome (age-adjusted rate ratio 0.83; IC 95% 0.74 a 0.92; P<0.001). The benefit was greater in the more severe patients who needed oxygen (n=3883; 21.5% vs. 25.0%, rate ratio 0.80 IC 95% CI 0.70 a 0.92; p=0.002) or mechanical ventilation (n=1007; 29.0% vs. 40.7%, rate ratio 0.65 IC 95% 0.51 a 0.82; p<0.001). These results were presented before the publication, and several institutions, such as the NHS and the NIH, changed their recommendation in favour of the use of dexamethasone (6 mg qd for 10 days).

The preliminary results of the RECOVERY trial made us change our original design for the usual care. In the beginning, this study sought to compare dexamethasone (higher doses than RECOVERY trial) versus usual care, without steroids. This approach is unfeasible nowadays, thus we modified our initial design to allow low dose dexamethasone for 10 days as usual care treatment. However, the dose proposed by the British study might not be enough to suddenly reverse the inflammatory changes in patients with ARDS.

In summary, there is evidence that a dysregulated inflammatory response in patients with COVID-19 pneumonia may cause ARDS with unfavorable prognosis. Many of them will require mechanical ventilation for long time, overcrowding the regional health system. The treatments of the severe COVID-19 pneumonia in unknown and randomized trials are needed to test their efficacy. The steroids, as unspecific anti-inflammatory agents, may shorten the respiratory failure and improve the prognosis. Low-lose dexamethasone reduced the risk of death in patients with oxygen needs, or mechanical ventilation. The aim of this study is to explore the effectiveness and safety of high-dose dexamethasone, against usual care, in the treatment of SARS-CoV-2 pneumonia, in patients with ARDS.

MATERIALS AND METHODS

TRIAL DESIGN

Multicenter randomized clinical trial, controlled, open, parallel group, to evaluate the effectiveness and safety of high dose dexamethasone in adult patients with confirmed COVID-19, with Acute Respiratory Distress Syndrome.

MAIN OUTCOMES

The main result is ventilator-free days at 28 days (Days without ventilator support in the first 28 days following randomization).

Secondary outcomes measures

• 28-days mortality (Dead rate within 28 days of randomization)

• 90-days mortality (Dead rate within 28 days of randomization)

• Frequency of nosocomial infections (number of ventilator-associated pneumonia, blood stream infection or candidemia in the first 28 days following randomization)

• Viral shedding (Frequency of positive PCR on nasopharyngeal swab 28 days after randomization)

• Serum C - reactive protein variation (10 days after randomization)

• SOFA variation (over the first 10 days after randomization)

• Use of prone position (Cumulative hours spent on prone position at 10 days after randomization)

• Delirium (Frequency of delirium at ICU discharge)

• Muscle weakness (mMRC score at ICU discharge)

PARTICIPANTS

We will include patients with SARS-Cov-2 pneumonia who develop acute respiratory distress syndrome, in several intensive care units (ICU) in Buenos Aires, Argentina.

Inclusion criteria:

- Men and women, with age ≥ 18 years old.
- Diagnosed SARS-CoV-2 infection, by PCR.
- Diagnosis of Acute Respiratory Distress Syndrome (hypoxemic respiratory failure not explained by cardiac disease + PaO2/FiO2 ratio < 300 with a Positive End-Expiratory Pressure ≥ 5 cm H2O + bilateral pulmonary infiltrates)(23)
- Need of mechanical ventilation in the last 72 hours
- Informed consent (next of kin/ legal guardian)

Exclusion criteria:

- Pregnant or breast-feeding women.
- Terminal disease (advance cancer; under palliative care; cardiovascular, respiratory, or renal disease with a life expectancy less ≤ 1 year).
- Therapeutic limitation (advance directives or do not resuscitate order)
- Severe immunosuppression (HIV infection, long-term use of immunosuppressive agents, active cancer).
- Patients under chronic treatment with glucocorticoids for other diseases (dose ≥ 8 mg prednisone, or equivalent)
- Participation in another study.

INTERVENTION AND COMPARATOR

Eligible patients will be randomized to receive standard ICU patient care (group 1) or standard ICU patient care plus high dose dexamethasone (group 2).

- Group 1: dexamethasone up to 6 mg/24 hours for 10 days + ventilatory, hemodynamic, nutritional, and antimicrobial support according to international guidelines.
- Group 2: dexamethasone 16 mg/24 hours for 5 days and dexamethasone 8 mg/24 hours for 5 days + ventilatory, hemodynamic, nutritional, and antimicrobial support according to international guidelines.

Standard ICU patient care will not be regulated by the protocol. However, it is suggest treating the patients according to the international guidelines for ARDS (24), antibiotics and hemodynamic support for COVID-19 infection (19,25). The following standards are recommended:

- Sepsis: prompt infection source identification and adequate antibiotic treatment
- Hemodynamic support: individualized resuscitation with fluids and vasopressors to achieve adequate perfusion (mean arterial pressure target: 65-75 mm Hg)
- Protective mechanical ventilation
  - Tidal volume: 6 ml/kg (ideal body weight)
  - Plateau pressure < 30 cm H_2_O, Driving pressure < 15 cm H_2_O
  - Respiratory rate to achieve PaCO_2_ 35-45 mm Hg
  - Minimal FiO_2_ to achieve SaO_2_ 88-94%
  - PEEP titration, according to ARDSnet trial (26), or Express maximal recruitment (27)
- Dexamethasone use: no more than 6 mg qd for ten days

Weaning protocol

The weaning protocol is defined by each site. We recommend evaluating the patients in a daily basis to perform a spontaneous breathing trial (SBT), based on the ARDSnet protocol, with a FiO_2_ <= 0.5. The following are the minimal pre-requisites to perform an SBT:

- PaO_2_/FiO_2_ > 200 con PEEP <= 10 cm H_2_O (>12 hours)
- Hemodynamic stability
- Minimal sedation (RASS> -1)
- Cough during aspiration maneuvers

The trial will be performed in pressure support ventilation (pressure support 8-10 cm H_2_0, and ZEEP, with a FiO_2_ <= 50%), if possible. If the test is passes successfully, the attending physician will decide, or not, to extubate the patient. This test can be done daily.

POSSIBLE CONFOUNDERS

The following variables will be evaluated as possible confounders:

- Age and gender
- Ventilatory mode, and parameters of mechanical ventilation
- Oxygenation variables (pH, PaO_2_, PaCO_2_)
- Severity scores (APACHE II (28), SOFA (29))
- Shock
- Co morbidities (Charlson score (30))

RANDOMISATION AND BLINDING (MASKING)

Treatment will be assigned according to site stratified randomization by permuted random blocks sequence 1:1 generated with a table in R language. The randomization table is concealed in the randomization tool of the REDCap (Research Electronic Data CAPture) platform.

This is an open trial, so no masking of treatment assignment will be used.

SAMPLE SIZE

Assuming a 3 days difference in ventilator-free days between treatment groups, with a mean of 9 days, and a standard deviation of 9 days; the necessary sample size would be 284 subjects (142 per group), with a power of 80% and a two-tailed alpha error of 0.05.

STATISTICAL ANALYSIS:

All tests will be on an intention-to-treat basis. Initially, a descriptive analysis will be performed. The different variables will be compared according to the treatment with usual statistical test according to data distribution (normality of data will be evaluated by Shapiro-Wilk test).

Main outcome variable analysis (ventilator free-days) will be compared by Wilcoxon test. A competing risk model will be done for the time to first successful extubation, adjusting for APACHE II score and ARDS severity. Two competing events (successful weaning and dead under mechanical ventilation) will be evaluated; sub-hazard ratio will be calculated by the Fine and Gray method.

Survival at 28 days will be evaluated by Cox regression analysis, with assigned treatment, APACHE II and ARDS severity as predictors. Change in different daily parameters (vital sign, SOFA score, chemistry, sedation, parameters of mechanical ventilation, among others) will be compared by a mixed-effect regression model (fixed and random), using the treatment as fixed variable and the patient code and the day of data acquisition as random. The same procedure will be performed for safety measures, using glucose levels and insulin requirements. Number of infections in the first 28 days will be analyzed with a Poisson model, with treatment, APACHE II score, and ARDS severity as predictors. A quasi-Poisson model, or a negative binomial, will be done in case of over-dispersion. In this case the results will be expressed to the best fit model, according to Akaike Information Criterion (AIC).

The analysis will be carried out with the statistical package R: A language and environment for statistical computing (R Core Team, R Foundation for Statistical Computing, Vienna, Austria. URL <http://www.R-project.org/>).

TRIAL REGISTRATION AND CURRENT STATUS

The trial was registered under the title “Dexamethasone for COVID-19 Related ARDS: a Multicenter, Randomized Clinical Trial” with ClinicalTrials number NCT04395105, registered on 20 May 2020. The protocol with code DEXA-ARDS-COVID19, version 3.0 on date: 13/MAY/2020 is already approved by the Local Research Ethics Committee of CEMIC. The trial is already in the recruitment phase.

ETHICS APPROVAL AND CONSENT TO PARTICIPATE

The protocol was evaluated by the Local Research Ethics Committee of CEMIC (Buenos Aires, Argentina), on May 13, 2020 with the reference code 1264. It was approved on May 13, 2020. The study was also approved by the SATI (Sociedad Argentina de Terapia Intensiva) Ethics Committee.

Patient’s next of kin will be asked for informed consent. This will be reflected in the medical record before included in the clinical trial. A copy of the informed consent will be attached in the medical record.

REFERENCES

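### The day-10 CRP outcome is not tied to one analysis rule, and neither candidate rule adjusts for baseline CRP; the mixed model as worded does not estimate a change or a day-10 difference

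*Protocol*

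**What the plan says.** Under Main Outcomes, the protocol's secondary list includes "Serum C - reactive protein variation (10 days after randomization". It does not say whether the variation is absolute, relative or logarithmic, or how often CRP is sampled.

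Under Statistical Analysis, two statements could govern this outcome:

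- A general rule: variables are to be "compared according to the treatment with usual statistical test according to data distribution (normality of data will be evaluated by Shapiro-Wilk test".
- A specific rule: "Change in different daily parameters (vital sign, SOFA score, chemistry, sedation, parameters of mechanical ventilation, among others) will be compared by a mixed-effect regression model". Its terms are then given: "using the treatment as fixed variable and the patient code and the day of data acquisition as random".

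CRP is named in neither. As a serum measurement it fits best under the second, where chemistry is listed and the list is left open. SOFA variation, the next outcome in the secondary list, is covered there by name. No baseline value appears as a covariate in either rule.

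**The concern.** A change outcome already requires a baseline measurement. If baseline is subtracted but not used as a covariate, its noise enters the comparison although treatment cannot have affected it. The mixed model raises a second problem: without a treatment-by-day term, its treatment coefficient is one average over the follow-up days, whereas the outcome is defined at day 10.

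CRP is the only inflammatory marker among the listed outcomes. The introduction's case for the higher dose is that the usual dose may not be enough to reverse the inflammatory changes of ARDS. A CRP comparison that is imprecise, or that answers a different question, could be read as evidence against that mechanism when it shows only a weak analysis.

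**Working it through.** **The plan's own figure.** The only sample-size figure is for ventilator-free days: "Assuming a 3 days difference in ventilator-free days between treatment groups", "a standard deviation of 9 days", 80% power, two-sided 0.05. Per arm, n = 2(1.960 + 0.842)² × 9²/3² = 2 × 7.85 × 9 = 141.3, so 142 per arm and 284 in total. This agrees with "the necessary sample size would be 284 subjects (142 per group". It says nothing about CRP.

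**What the mixed model estimates.** With treatment as the only stated fixed effect and patient and day as random, there is a single treatment coefficient for all days. If the response is the CRP value, this is a difference in level averaged over days. If the response is the change from baseline, it is an average change. Neither is a day-10 contrast.

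As an illustration, assume CRP measured daily on days 0 to 10 and a true day-10 ratio of 0.70 (log effect 0.357).

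- Effect growing linearly from zero, day 0 included: the average log effect is half, 0.178, which is a ratio of √0.70 = 0.84.
- Effect growing linearly, days 1 to 10 only: 0.55 × 0.357 = 0.196, a ratio of 0.82.
- Full effect from day 1, day 0 included: (10/11) × 0.357 = 0.324, a ratio of 0.72.

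The coefficient would thus show a reduction of about 16 to 28% where the day-10 reduction is 30%. It matches 30% only if the effect is immediate and day 0 is left out.

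**What the missing baseline covariate costs on the log scale.** The protocol gives no CRP SD, correlation or effect, so all inputs are assumptions: log SD s0 = 0.6 to 0.9 at entry, s1 = 0.9 to 1.0 at day 10, correlation r = 0.2 to 0.5, day-10 CRP 30% lower in Group 2 (δ = −ln 0.70 = 0.357), and 100 per arm with a day-10 value.

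- Baseline-adjusted variance: s1²(1 − r²)
- Unadjusted change variance V: s0² + s1² − 2·r·s0·s1
- Power ≈ Φ(δ/√(2V/100) − 1.96), with the relevant variance as V

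| s0 | s1 | r | Adjusted variance | Change variance | Ratio | Power, adjusted | Power, change |
|---|---|---|---|---|---|---|---|
| 0.6 | 0.9 | 0.2 | 0.778 | 0.954 | 1.23 | 82% | 73% |
| 0.6 | 0.9 | 0.5 | 0.608 | 0.630 | 1.04 | 90% | 89% |
| 0.6 | 1.0 | 0.2 | 0.960 | 1.120 | 1.17 | 73% | 66% |
| 0.6 | 1.0 | 0.5 | 0.750 | 0.760 | 1.01 | 83% | 82% |
| 0.9 | 0.9 | 0.2 | 0.778 | 1.296 | 1.67 | 82% | 60% |
| 0.9 | 0.9 | 0.5 | 0.608 | 0.810 | 1.33 | 90% | 80% |
| 0.9 | 1.0 | 0.2 | 0.960 | 1.450 | 1.51 | 73% | 55% |
| 0.9 | 1.0 | 0.5 | 0.750 | 0.910 | 1.21 | 83% | 75% |

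Simulation under the same assumptions gave about 69 to 90% (adjusted) and 55 to 90% (change), in line with the formula apart from simulation error.

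**The raw scale.** For medians falling from 150 to 50 or from 120 to 80 mg/L, otherwise as above, simulated power of a rank test on the raw change was 17 to 69%. Most of that loss comes from the raw scale of a skewed, falling marker. The missing covariate alone accounts for at most about 22 points in the table (82% to 60%).

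**The case against.** The strongest reply is that scale, transformation and covariates for one secondary laboratory outcome are commonly left to a SAP, and a SAP may exist that is not shown. That stands as a reason to rate the point low. It does not remove it, because the protocol goes beyond leaving the matter open: it writes out the terms of the mixed model, and those terms do not yield the outcome it names.

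A reader might infer three stronger claims, and the documents do not support them.

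- *That the plan is a Shapiro-Wilk-chosen test of raw CRP change.* The rule on daily parameters more naturally covers a serum value, and the protocol nowhere says that the variation is on the raw scale.
- *That most of the power is lost.* This arises only under the raw-scale rank test with assumed inputs, and not throughout its range (up to 69% power). On the log scale the variance ratio runs from 1.01 to 1.67, so omitting the covariate may cost almost nothing.
- *That the Shapiro-Wilk step should be removed throughout the trial.* The CRP evidence does not reach that far. Validity is not at issue either: in a null simulation the type I error was 4.5 to 5.7% both for the rank test on raw change and for the adjusted log analysis.

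A further fair point is that a repeated-measures model can use earlier values from patients who die or leave before day 10, whereas a regression on day-10 values alone cannot. This favours repairing the mixed model over replacing it.

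**Conclusion.** The point holds in a narrow form. The protocol does not clearly assign CRP to a rule. Neither candidate adjusts for baseline, and the mixed model as worded answers a question about the average over days when the outcome is defined as a variation at day 10. That mismatch follows from the text alone.

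The size of the power loss does not. Under the stated assumptions it is about 1 to 22 percentage points for an unadjusted log change, and larger only if raw change is rank-tested. Severity is minor: one secondary outcome is affected, and the primary comparison is untouched.

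**What to change.** State which rule governs CRP, and word it as follows. Keep the mixed model for CRP, applied to log CRP at post-baseline days, with baseline log CRP, day, treatment and treatment-by-day as fixed effects and patient as random. Report the day-10 ratio of geometric means with a 95% CI. If CRP is sampled only at baseline and day 10, regress day-10 log CRP on treatment and baseline log CRP and report the same ratio.

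This is a change of wording and needs no new data, since a variation cannot be computed without the baseline value. The costs are that the result is a ratio and not a difference in mg/L, that values below the assay limit need a stated floor, and that the day-10-only regression drops patients without a day-10 sample.

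### Delirium, muscle score and day-28 PCR have no value in patients who die first, so the planned test compares survivors and is not the intention-to-treat comparison the protocol claims.

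*Protocol*

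**What the plan says.** The protocol's list of secondary outcomes ties three of them to a moment that some patients will not reach:

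- "Delirium (Frequency of delirium at ICU discharge"
- "Muscle weakness (mMRC score at ICU discharge"
- "Viral shedding (Frequency of positive PCR on nasopharyngeal swab 28 days after randomization"

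The Statistical Analysis section opens with "All tests will be on an intention-to-treat basis". It gives no model for these three outcomes, so they fall under the general rule: "The different variables will be compared according to the treatment with usual statistical test according to data distribution". Death is treated as a competing event in one analysis only, time to first successful extubation: "Two competing events (successful weaning and dead under mechanical ventilation) will be evaluated". Mortality is an outcome in its own right at 28 and 90 days, and 28-day survival has a Cox model.

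**The concern.** A patient who dies in the ICU has no delirium or muscle assessment at ICU discharge. A patient who dies before day 28 has no swab. Applied as written, the general rule therefore tests the two groups of survivors. Randomisation made the full arms comparable. It does not make the survivors comparable if the dose affects survival, and the protocol's rationale is that steroids may improve prognosis.

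What may be concluded is at stake. Suppose the high dose saves some very sick patients who then leave the ICU delirious or weak. The survivor comparison shows an excess on the high dose even if the drug has no effect on delirium or strength. Suppose instead that it costs lives among the sickest. The same comparison then flatters it. The trial is open-label, so a rule for deaths chosen late could be chosen with the results in view.

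**Working it through.** **Plan's own figure.** The sample size section assumes a difference of 3 days, SD 9, 80% power and two-sided alpha 0.05:

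n per arm = 2 × (1.96 + 0.84)² × 9² / 3² ≈ 141.3, rounded up to 142, total 284.

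This reproduces the protocol. It concerns ventilator-free days and does not depend on the present point.

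**How many patients could lack a value.** The protocol's Introduction cites hospital mortality of 21% v 36% (dexamethasone v placebo in ARDS) and 28-day mortality of 29.0% v 40.7% (6 mg dexamethasone v its comparator, ventilated COVID-19 patients). Both arms here may receive steroid, so the nearest cited rate for the low-dose arm is 29.0%: 142 × 0.29 ≈ 41 patients. At 36% it would be 142 × 0.36 ≈ 51. Neither source gives ICU mortality, which governs the two ICU-discharge outcomes.

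**Model for the bias.** Let Sc and St be survival on low and high dose, with St > Sc. Let pa be the delirium risk in patients who survive on either dose and ps the risk in those who survive only on the high dose. The drug has no effect on delirium itself.

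- Survivor delirium, low dose: pa
- Survivor delirium, high dose: [Sc × pa + (St − Sc) × ps] / St
- Spurious gap: (St − Sc)/St × (ps − pa)

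The protocol gives no delirium rates, so pa = 30% and ps = 70% are assumptions. The 26% mortality on the high dose is also assumed.

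| Mortality, low v high | Survivor delirium, low | Survivor delirium, high | Spurious gap | Gap for ps from 50% to 90% |
|---|---|---|---|---|
| 29% v 26% | 30.0% | (0.71 × 0.30 + 0.03 × 0.70)/0.74 = 31.6% | 1.6 points | 0.8 to 2.4 |
| 36% v 26% | 30.0% | (0.64 × 0.30 + 0.10 × 0.70)/0.74 = 35.4% | 5.4 points | 2.7 to 8.1 |

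If ps = pa, or if the dose does not change who survives, the gap is zero. If the high dose is the one with 36% mortality, the second row turns into an apparent benefit of 5.4 points.

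**Would the test flag it?** In the second row there are about 91 v 105 survivors, and the chance of p < 0.05 in either direction is about 13% (7% at ps = 50%, 22% at ps = 90%), against 5% with no gap. In the first row (about 101 v 105 survivors) it is about 6%.

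**What a composite does.** Alive and delirium-free, all randomised, at 36% v 26%:

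- No drug effect on delirium: 0.64 × 0.70 = 44.8% v 0.448 + 0.10 × 0.30 = 47.8%. The direction reverses, because the composite counts the lives saved.
- A true rise from 30% to 35% in patients who survive on either dose: 44.8% v 0.64 × 0.65 + 0.10 × 0.30 = 44.6%. The real harm disappears.

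So neither comparison is sufficient alone.

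**The case against.** The strongest reply is that the protocol is only silent. It never says survivor-only, intention-to-treat can mean no more than analysis by assigned arm, and a statistical analysis plan that is not shown may settle how deaths enter each outcome. Part of this stands: a separate plan could supply a rule. But the protocol itself fixes outcomes that are undefined for the dead, names the default test and puts all tests under one intention-to-treat label. Any later rule would have to redefine the outcomes or narrow that label.

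The objection to the size stands in full. The cited mortality gaps come from steroid against placebo or no steroid, while this trial compares a higher with a lower dose, so the gap here may be much smaller. The delirium risks are assumed. A reader might infer that these tests will report harm from a dose that only saves lives; the figures do not support that, since in the illustrations the test usually shows nothing.

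A reader might also infer that these three outcomes are the trial's main safety questions. The protocol's named safety measures are glucose and insulin requirement, and infections are modelled separately. Mortality is also analysed, so a difference in deaths would be visible beside these results.

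Finally, a composite is a trade-off and not a cure. It can mask a real effect, as shown above, and should not become the sole test.

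**Conclusion.** The point holds in a limited form. For these three outcomes the planned test compares survivors, and the intention-to-treat label cannot be supported. Bias arises only if the dose changes who survives and the patients saved differ in risk from the other survivors; it can then go in either direction. Its size cannot be fixed from the protocol: about 1.6 points at 29% v 26% mortality and about 5 points at 36% v 26% under the assumed delirium risks, and zero under equal risk. If delirium at ICU discharge were read as any episode during the stay, patients who die could contribute, but the wording places the assessment at discharge, and the muscle score and day-28 swab allow no such reading. Severity is low to moderate: these are secondary outcomes, and neither the primary analysis nor the 284 patients is affected.

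**What to change.** Make three changes of wording, in the protocol or the statistical analysis plan, before outcome data are examined by arm:

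1. State that between-arm comparisons of these three outcomes among survivors are descriptive and carry no causal or intention-to-treat claim.
2. For each outcome, report by arm the numbers dead, alive and assessed, including living patients who were not swabbed at day 28.
3. Add a supportive analysis of all randomised patients: proportion alive and delirium-free at ICU discharge; muscle score compared by ranks with ICU deaths ranked worst; proportion alive and PCR-negative at day 28, with a stated rule for living patients not swabbed. Read these beside mortality and the survivor figures.

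The cost is analysis wording and a few table rows; no new data are needed. The downside is that the composites partly reflect mortality and can hide a real effect on the component, so they supplement the survivor figures and do not replace them.
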